### Outcome measures

Measurements are collected on all study households (household questionnaire) and participants (mother and child questionnaire) at month 0, 1, 2, 3, 4, 5, 6 and 12. Measurements are collected during the week following the receipt of each transfer. The primary outcomes are prevalence of wasting (as measured by WHZ < −2 or the presence of bilateral pitting oedema) and mean WHZ score in children.

Secondary outcomes are:in children - cumulative incidence of wasting, prevalence of SAM (<−3 WHZ), low mid-upper arm circumference (MUAC) (<125 mm & < 115 mm), stunting (<−2 height-for-age z-score) and morbidity (mainly diarrhoea, difficulty breathing/cough, malaria)in mothers and children - mean haemoglobin concentration (Hb g/dL) and prevalence of anaemia (children: Hb <11.0 g/dL; severe anaemia as Hb < 7.0 g/dL; non-pregnant women Hb <12.0 g/dL; pregnant women Hb <13.0 g/dL)in mothers - prevalence of low body mass index (<16, <17, <18.5 kg/m^2^), low height (<145 cm) and low MUAC (<230 mm & <210 mm).

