### Sample size

To determine the minimum detectable difference in prevalence of wasting for this sample size the following information was used: 1) estimated prevalence of wasting at baseline (16 %); 2) an estimate of the intra-class correlation coefficient (ICC) from a previous survey (0.02); 3) an estimate of the average cluster size (50); 4) for unequal cluster sizes an estimate of the coefficient of variation of cluster sizes (0.65); 5) significance level at 5 % and power of at least 80 %; 6) a likely dropout rate of 10 %; and 7) the estimated number of eligible children per household (2.2).

The sample size is 632 households per intervention group. This sample size is sufficient to measure a detectable difference of 7 % between the intervention groups and the comparison group post intervention. The sample is powered to detect a 0.19 WHZ difference between the intervention and comparison groups (based on a baseline mean of −1.22 (1.10), from previous data).

Sample size calculations were carried out in Stata (SE version 13.1; StataCorp, Special Edition, College Station, Texas 77845 USA) using the [*clustersampsi*] command.

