### Planned statistical analysis

The study will use both quantitative and qualitative data analytical methods and a cost-effectiveness analysis will be done. The key steps for the quantitative data analysis of outcome measurements will be: 1) cluster level analyses using summary measures between the different time points and 2) individual level analyses adjusted for clustering (longitudinal generalised mixed models). Significance will be assessed at *p* < 0.05 level.

Baseline descriptive analyses will be carried out on all independent variables at cluster and individual levels to assess baseline differences between groups. The data will be examined for outliers, normality and missing data. To test the overall effect of the interventions (on an intention-to-treat basis), changes in outcome variables between the different groups over follow-up measurements (6 months and at 1 year) will be compared. The interventions, measurement time and intervention-time interaction will be included as fixed effects in the models. Children, mothers and villages will be included as random effects in the intercept and in the slope of the different repeated measurements. Potential confounders (e.g. sex, age and baseline nutrition status) will be used if there are differences at baseline. Best fit of the data will be assessed using maximum likelihood ratio tests.

We will examine the data to determine the extent and type of differential attrition, and depending on our findings, we may apply an appropriate adjustment to estimates of intervention effect and/or discuss the possible consequences they may have on the reliability of the estimates. Since there will be more than one child per household in many cases, a secondary analysis using one child per household (selected at random) will be carried out to confirm if results are being driven by a smaller number of larger households. A mediation analysis (using seeming unrelated regression methods [22–24]) will be carried out to measure the extent to which increased mediating variables may mediate the relationship between the different interventions and comparison group and wasting. All quantitative analyses will be carried out in Stata 13.1. Z-scores will be generated using the World Health Organisation (WHO) macro for Stata.

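### The mediation analysis names only yes/no wasting as its outcome; fitting it to continuous WHZ as well would recover information that the cut at −2 discards

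*Protocol article*

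**What the plan says.** The protocol article's Planned statistical analysis gives mediation one sentence. It names the method: "A mediation analysis (using seeming unrelated regression methods [22–24]) will be carried out". It also names the target, namely how far intermediate variables "may mediate the relationship between the different interventions and comparison group and wasting". No other outcome is mentioned for this analysis. The sentence does not state a coding, a link function or a variance estimator; the detail is left to three references.

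Outcome measures sets the two child outcomes side by side: "The primary outcomes are prevalence of wasting (as measured by WHZ < −2 or the presence of bilateral pitting oedema) and mean WHZ score". Wasting is therefore binary and WHZ continuous, and both are primary. Table 2 shows child weight, height and oedema recorded at baseline, months 1 to 6 and month 12, so WHZ is available wherever wasting is.

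Study design says that children are the unit of analysis and that village clustering is taken into account.

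**The concern.** Seemingly unrelated regression, named without qualification, is a system of linear equations and is most natural for a continuous outcome. The article has such an outcome in WHZ, yet the mediation sentence points only to the version cut at −2. Cutting a continuous measure discards information, and an indirect effect is a product of two paths, so it is usually harder to estimate than a total effect.

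Explaining how the transfers work is an express purpose in the Abstract and in the third and fourth study aims. Mediation is the only quantitative method that the analysis section names for testing pathways. A test weaker than the data allow makes it more likely that a real pathway is estimated too imprecisely to be recognised.

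**Working it through.** **Inputs.** From Sample size: wasting 16%; WHZ "baseline mean of −1.22 (1.10), from previous data"; ICC 0.02; mean cluster size 50; coefficient of variation of cluster size 0.65; 5% significance (taken as two-sided); 80% power; 10% dropout; 2.2 eligible children per household; 632 households per group; detectable differences of 7 points and 0.19 WHZ. The article gives no mediator effects.

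**Reproducing the plan's figures.** The design effect is 1 + ((1 + 0.65²) × 50 − 1) × 0.02 = 2.4025. Comparing 16% with 23% needs 502 children per arm. 502 × 2.4025 = 1206, or 25 whole clusters = 1250 children, and 1250 / 0.9 / 2.2 = 631.3, so 632 households. Going back, 632 × 2.2 × 0.9 = 1251 children, with an effective number of 1251 / 2.4025 = 521. The detectable WHZ difference is (1.960 + 0.842) × 1.10 × √(2/521) = 0.19. The stated figures reproduce, so these inputs are a sound base.

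**Information kept by the cut.** For a small shift in a normal variable cut so that a proportion p lies below the threshold, the information kept is φ(z_p)² / [p(1 − p)].
- At p = 0.16: z = −0.994, φ = 0.243, and 0.0592 / 0.1344 = 0.44, a loss of 56%.
- At the p implied by the WHZ mean and SD: z = (−2 + 1.22) / 1.10 = −0.709, p = 0.239, φ = 0.310, and 0.0963 / 0.1819 = 0.53, a loss of 47%.

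The article's two inputs imply different prevalences, so both are shown as a range. At lower prevalences less is kept (0.32 at 9%).

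**Cross-check with a finite shift.** For an improvement of 0.19 WHZ, before the design effect, WHZ needs 527 children per arm. Binary wasting needs 1047 starting from 23.9% (ratio 0.50) or 1285 starting from 16% (ratio 0.41). This agrees with about half.

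**From the outcome equation to the indirect effect.** Write a for the intervention-to-mediator effect and b for the mediator-to-outcome effect. In the Sobel form, 1/z²_ind = 1/z²_a + 1/z²_b. The cut multiplies only z²_b, by 0.44 or 0.53.
- Path a limits precision: 1/z²_a dominates and the loss is near 0.
- Equal precision: 2 / (1 + 1/0.44) = 0.61, a loss of 39%; 2 / (1 + 1/0.53) = 0.69, a loss of 31%.
- Path b limits precision: the loss approaches 56% or 47%.

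**Power, under assumed mediator effects.** A simulation used 25 analysed villages per arm with the article's cluster size, variation and ICC, village-clustered standard errors, and a test requiring both paths to be significant. It assumed a = 0.3 SD and b = 0.06 to 0.10 SD per SD. Power was 73–96% with WHZ, against 43–84% (16% wasted) or 51–88% (24% wasted) with wasting. Like for like, the gain was 8 to 30 points.

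That gain depends on a. With 50 / 2.2 = 22.7 households per village, the design effect for a household-level mediator is 1 + ((1 + 0.65²) × 22.7 − 1) × 0.02 = 1.63. The effective number is 25 × 22.7 / 1.63, about 349 per arm, and the standard error of a is √(2/349) = 0.076 SD. Power for path a alone is then about 98% at 0.3 SD, 51% at 0.15 and 26% at 0.10. Treating the paths as independent and rescaling, the gain falls to about 4–16 points at 0.15 and 2–8 points at 0.10.

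**The case against.** The strongest reply is that wasting is a legitimate target. It is the first-named primary outcome, the main basis of the sample size and the outcome for cost-effectiveness. It also counts oedema, which WHZ does not. Which primary outcome to explain is a choice of estimand. This stands, and it is why WHZ should be added and wasting kept.

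It can also be said that one summary sentence fixes neither the coding nor the model. The Background uses wasting for the condition in general, WHZ is not excluded, and probit versions of such systems exist. This stands in part: a reader might infer that the analysis is locked to a linear model of a binary variable, and the text does not go that far. Yet wasting is the only outcome named and the article defines it as binary. A probit form would not recover the information lost by the cut.

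A reader might further infer that the standard errors would be invalid because a linear model of a 0/1 outcome has non-constant variance. The article does not support this. It nowhere says that default standard errors will be used, and Study design promises allowance for village clustering. Village-clustered errors also deal with non-constant variance.

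Finally, the efficiency ratio assumes a uniform shift in a normal WHZ. If transfers mainly help children near or below −2, the ratio does not apply. That limit is real.

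**Conclusion.** The point holds as a moderate, inexpensive improvement. The mediation sentence names only a yes/no outcome although a continuous primary outcome suited to the stated method is already collected. Under normality and a small uniform shift, the cut keeps about 44–53% of the information in the mediator-to-outcome equation.

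It would be tempting to say that the whole pathway analysis loses half its information. That is only the upper end: for the indirect effect the loss lies anywhere from near 0 to 47–56%, depending on which path limits precision. Nor can the 8 to 30 point gain in power be taken as the expected benefit, since it rests on one assumed mediator shift of 0.3 SD and shrinks as that shift shrinks.

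The aim is to measure the extent of mediation, so lower precision widens intervals; it does not make the conclusion wrong. The question of how the transfers work is also addressed by the process evaluation and the qualitative study. The primary analyses are unaffected.

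**What to change.** Amend the mediation sentence in Planned statistical analysis so that the seemingly unrelated regression is fitted with WHZ as an outcome, with standard errors or bootstrap resampling by village. Keep wasting beside it, fitted either by a binary-outcome mediation method or as a linear probability model with village-clustered standard errors, and say which.

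The cost is a change of wording and one more analysis, with no new data. The WHZ result will be in Z-score units and will not capture oedema; the retained wasting analysis covers both points.

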## Discussion

With an increasing interest and use of cash-based programming in humanitarian settings to prevent acute malnutrition, it is of high priority to determine what works best and in what context. The lack of current evidence makes it difficult for decision-makers to ensure the best strategies are used in terms of impact and sustainability. In terms of establishing what works, or doesn’t, requires unpacking the theory of change as well as exploring the processes involved in order to determine where the opportunities and barriers lie.

The present study protocol describes a theory informed cluster randomised controlled trial of three cash-based interventions, randomised among villages with the main objective of maintaining and improving the nutritional status of children less than five years of age throughout the lean period and after 1 year in Dadu District. This study will also provide detailed information on both delivery and use of the intervention. The results of this study will furthermore provide robust evidence to help increase understanding of how and why certain modalities of cash transfers work better than others in a defined humanitarian setting. Findings from the cost-effectiveness analysis will contribute to an understanding of which intervention provides greater value for money in this context, and will provide information on resource use of these intervention strategies by both institutions and beneficiary households in Pakistan. Furthermore, this study will provide important evidence to bridge our gap in understanding the cost-effectiveness of cash interventions in achieving nutrition objectives.

### Trial status

Recruitment closed. Trial on-going.

## Abbreviations

ACF: Action Against Hunger
ABC: Activity-based costing
cRCT: Cluster randomised controlled trial
CEA: Cost-effective analysis
DFID: Department for International Development
ECHO: EU Humanitarian Aid and Civil Protection
ENN: The Emergency Nutrition Network
EU: European Union
GAM: Global acute malnutrition
Hb: Haemoglobin
HEA: Household Economy Approach
ICC: Intra-class correlation coefficient
ICER: Incremental cost-effectiveness ratios
ICN: Individual case narratives
MUAC: Mid-upper arm circumference
ODK: Open Data Kit
PKR: Pakistan Rupees
QRTS: Qualitative research tracer study
SAM: Severe acute malnutrition
WASH: Water, sanitation and hygiene
WHZ: Weight-for-height Z-score
WHO: World Health Organisation
